### Assessment

2.8

Assessments take place before the onset of the intervention period (T0), 1 week (T1), 2 weeks (T2), 4 weeks (T3) after the intervention has started, and at the end of the intervention (6 weeks after start of the intervention; T4). Follow-up will take place at 12 weeks after the end of the intervention (T5) (Table 1). Each assessment consists of an online questionnaire and a telephone interview. Except HDRS17, the EPDS, WHOQOL and SMCDS are self-report scales, which will be filled out online at T1-T5. The access of online questionnaires will be sent to subjects by researchers in charge of assessment, at the assessment nodes after inclusion. HDRS17 will be assessed by researchers through telephone interview with subjects.

**Table 1 tab1:** Overview of assessment points and measurements used.

	Online screening	Face-to-face interview	T0	T1	T2	T3	T4	T5
			-7 ~ 0d	1w ± 3d	2w ± 3d	4w ± 3d	6w ± 3d	12w ± 3d
In−/exclusion criteria	×							
Witten consent form		×						
Sociodemographic information		×						
Regular health education			×	×	×	×	×	
Internet-based peer education			×	×	×	×	×	
Edinburgh Postpartum Depression Scale			×	×	×	×	×	×
17-item Hamilton Depression Rating Scale			×	×	×	×	×	×
World Health Organization Quality of Life Scale Brief			×	×	×	×	×	×
Self-Efficacy to Manage Chronic Disease Scale			×	×	×	×	×	×
Medical history, medication, therapies		×	×	×	×	×	×	×
Adverse event		×	×	×	×	×	×	×
Assessment of adherence		×	×	×	×	×	×	×
Completion assessment		×	×	×	×	×	×	×
Review by investigator		×	×	×	×	×	×	×

### Sample size

2.9

The sample size has been calculated according to the results from a previous clinical trial (27). The primary outcome in present study is the response rate at the end of 6-week intervention. Referring to the study of Uebelacker et al. (27), the response rate of health education group is 28.3% (responders). This study assumed that the effective rate of IPE combined with RHE was 70%. A two-sided test is required (25), *α* = 0.05, the sample size ratio of the two groups N1: N2 = 1:1 (i.e., the number of cases in the two groups is equal), *β* = 0.2, and the power of the test is 1-*β* = 80%. The analysis result is N1 = N2 = 38 cases, and 44 cases are included in each group according to the dropout rate of 15%. Therefore, a total of 44 patients/group ×2 groups = 88 patients will be included in this study.

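### Section 2.9: the stated rates, alpha and power give about 22 patients per arm, not the stated 38, so at least one stated figure is misreported

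*Protocol article*

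**What the plan says.** Section 2.9 of the Protocol article gives both the inputs and the result of the sample-size calculation in one paragraph.

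- **Endpoint:** "The primary outcome in present study is the response rate at the end of 6-week intervention".
- **Control arm**, taken from an earlier trial: "the response rate of health education group is 28.3% (responders".
- **Intervention arm:** "This study assumed that the effective rate of IPE combined with RHE was 70" (per cent).
- **Error rates and allocation:** "A two-sided test is required", with alpha 0.05, beta 0.2 (80% power) and 1:1 allocation.
- **Result:** "The analysis result is N1 = N2 = 38 cases, and 44 cases are included in each group". The step from 38 to 44 is attributed to 15% dropout, for a total of 88.

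The paragraph names no formula or software for this calculation. It mentions no continuity correction, allowance for clustering or adjustment for multiplicity. Section 2.10 plans a chi-square test for between-group comparisons of categorical data.

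**The concern.** Two response rates, alpha, power and allocation ratio fix the sample size to within the small differences between standard formulas. If the reported N lies well outside that range, the reported figures cannot all be true together.

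Section 2.9 is the trial's only stated justification for 88 patients, and it concerns the primary outcome. As written, it tells the reader that 38 evaluable patients per arm give 80% power for a difference of 70 − 28.3 = 41.7 percentage points. If 38 and 80% are right, the design effect is nearer 32 points. If 38 and 41.7 points are right, the power is well above 80%. The reader cannot tell which design was intended.

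**Working it through.** **Inputs (all from section 2.9).** p1 = 0.283, p2 = 0.70, difference d = 0.417, mean rate p̄ = 0.4915; z = 1.960 for two-sided 5% and 0.8416 for 80% power; equal arms.

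**Step 1. Attempt to reproduce 38.**

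Pooled chi-square formula: n = [1.960·√(2p̄(1−p̄)) + 0.8416·√(p1(1−p1) + p2(1−p2))]² / d²

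- √(2 × 0.4915 × 0.5085) = 0.7070, times 1.960 = 1.3857
- √(0.2029 + 0.2100) = 0.6426, times 0.8416 = 0.5408
- n = (1.9265)² / 0.1739 = 3.711 / 0.1739 = 21.3, so **22 per arm**

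Other standard methods on the same inputs:

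| Method | n per arm |
|---|---|
| Unpooled variance | 18.6, so 19 |
| Arcsine | 21.2, so 22 |
| Log odds ratio | 24.1, so 25 |
| Continuity-corrected | 25.9, so 26 |
| Fisher's exact, by enumeration | about 25 to 27 |

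The range is 19 to 27. The stated 38 is 38/22 = 1.73 times the chi-square result and 38/26 = 1.46 times the continuity-corrected one. Rounding or choice of software does not explain a gap of that size.

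**Step 2. Power that 38 per arm gives at the stated rates.**

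z = (0.417 × √38 − 1.3857) / 0.6426 = 1.844, so power is 96.7%. Exact binomial enumeration gives 96.6% for the uncorrected chi-square test and 94.3% for Fisher's exact test. These figures assume independent patients.

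**Step 3. Which single change would produce 38?**

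| Change to the stated inputs | n per arm |
|---|---|
| IPE rate 60%, 80% power, no correction | 37.3, so 38 |
| IPE rate about 62.5%, 80% power, continuity correction | 38 |
| Control rate about 38%, IPE 70%, 80% power | 37 |
| 28.3% vs 70%, 95% power, no correction / continuity correction | 35 / 39 |

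At 38 per arm, 28.3% versus 60% has exact chi-square power of 80.9%. The 60% rate fits neatly, but other changes reach 38 or come within a patient of it. The arithmetic does not identify the wrong input.

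**Step 4. Dropout step.**

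38 / (1 − 0.15) = 44.7, so 45 per arm. The stated 44 matches 38 × 1.15 = 43.7. With 15% loss, 44 × 0.85 = 37.4 remain, about half a patient short of 38. At the stated rates the formula power is 96.3% with 37 and 96.7% with 38.

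**Step 5. How far does independence matter?**

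Section 2.6.1.2 delivers IPE in WeChat groups of at most 11, so 44 patients form 4 groups, with 38/4 = 9.5 evaluable each. The documents give no intraclass correlation (ICC), so the values here are assumptions. Take clustering in the IPE arm only, with design effect D = 1 + 8.5 × ICC. Replace 2p̄(1−p̄) by (1 + D)·p̄(1−p̄), and p2(1−p2) by D·p2(1−p2), in Step 2.

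| Assumed ICC | D | Power, 38 per arm, 28.3% vs 70% |
|---|---|---|
| 0 | 1.00 | 97% |
| 0.05 | 1.43 | 93% |
| 0.10 | 1.85 | 88% |
| 0.20 | 2.70 | 78% |

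This is a rough approximation with only four groups. It shows why a restated power needs the independence caveat. It does not explain 38, because section 2.9 makes no allowance for clustering.

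**The case against.** The strongest reply is that the error is on the safe side. At the stated rates, 38 per arm gives 94–97% power, no patient number has to change, and the estimate, the test and the conclusion do not depend on section 2.9. A null result will be read mainly from the confidence interval for the observed difference. All of this stands and limits the weight of the point, but it does not reconcile the stated figures.

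Four stronger readings are tempting, and the documents do not support them.

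- **That the trial is underpowered.** A reader who sees a faulty calculation might infer this. For the stated effect the reverse holds, under independence.
- **That the intended IPE rate was 60%.** That figure is back-solved from 38, and Step 3 shows other routes to much the same N. The control rate rests on a cited trial that is not available here.
- **That 22 per arm would suffice, so the trial enrols too many.** This assumes that 70% and 80% are the correct inputs, which is the open question, and that patients within a WeChat group respond independently.
- **That a larger trial would be planned from wrong figures.** The abstract's conclusion and section 4 say that the follow-on trial will be informed by this trial's results, not by the assumptions in section 2.9.

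The dropout shortfall is about half a patient per arm, and section 2.10 plans multiple imputation for missing data. It is a side remark only.

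**Conclusion.** The inconsistency is established. On its own inputs, section 2.9 should report about 22 per arm (19 to 27 across standard methods) and reports 38. At least one of the stated rates, the power or the N is therefore misreported, and the document does not show which.

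The conclusion that 38 does not follow rests only on figures in section 2.9 and on standard two-proportion methods. The 94–97% power at 38 per arm also assumes independent patients, and would be lower if outcomes cluster within WeChat groups. The match between 38 per arm, 80% power and an IPE rate of about 60% is a description of the arithmetic, not evidence of what was planned.

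This is a moderate reporting error in a core design statement, in the safe direction for the stated effect.

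**What to change.** Keep 88 patients. Recover the original calculation and correct section 2.9 so that the two rates, alpha, power, formula (with software and any continuity correction) and N agree.

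- **If 28.3% versus 70% is confirmed:** state that 38 evaluable per arm give about 94–97% power (Fisher's exact test to chi-square), and that this ignores any clustering within the WeChat groups.
- **If another rate or power was used:** state that one.
- **If the calculation cannot be recovered:** say that 38 does not follow from the listed inputs. Do not enter 60% merely because it reproduces 38. Recruitment was due to end before March 2025, and a back-solved value would rewrite the design rationale after the fact.

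In the same edit, note that 15% dropout from 44 leaves about 37 evaluable per arm, or that 38/0.85 rounds up to 45.

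The cost is a look at the original calculation and a few sentences in section 2.9. No extra patients and no change to trial conduct or analysis are needed.

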### Statistical analysis plan

2.10

The statistical analysis will be conducted by independent statisticians who will be blinded to group allocation and intervention methods. Before data analysis, the research group will draw up a statistical plan, including the required data and method of data processing. For Categorical data, we performed the Chi-square (x^2^) test for between-group differences. For continuous and normally distributed data, we performed Student’s *t*-test for between-group differences and paired t test for within-group differences. If data were distributed nonnormally, the Mann–Whitney U test for between-group differences and the Wilcoxon test for within-group differences would be used. The normally distributed data were expressed as the mean ± standard deviation. Nonnormally distributed data would be expressed as the median or interquartile range (IQR). For categorical variables, the X^2^ test will be used to examine the between-group differences, and percentages and frequencies will be presented to describe the effect size.

For longitudinal data analysis considering the repeated measurements at assessment nodes in this study, the Generalized Estimating Equations (GEE) model will be employed.

Fixed effects structure: It will include the group variable (experimental vs. control), time points (six assessment nodes as a categorical variable), and the interaction term between group and time points. Additionally, potential confounding variables (e.g., baseline characteristics that show imbalance between groups) will be incorporated into the model as covariates to adjust for their effects.

Correlation structure: Given the repeated measurements within individuals over time, the exchangeable (compound symmetry) correlation structure will be initially assumed, which posits that the correlation between any two measurements from the same individual is equal. Sensitivity analyses will be conducted using other correlation structures (e.g., autoregressive of order one, which assumes a higher correlation between measurements that are closer in time) to assess the robustness of the results. The working correlation matrix will be estimated based on the observed data during model fitting.

All clinical data analyses will be performed using SPSS V.22.0 software. Missing data will be handled using the multiple imputation method. A two-tailed test will be conducted, and a *p* < 0.05 will be considered statistically significant.

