Through online forums, instant messaging, and pre—recorded videos, they can disseminate information, share their personal experiences, and provide continuous motivation to those in need, regardless of physical location.

So the integration of internet services into mental health care has shown notable developments, particularly in leveraging digital platforms to address various psychological issues. Studies have explored the impact of internet use on mental health, with research on older adults indicating that internet engagement can influence psychological wellbeing through mechanisms like social equity perception (21), while also highlighting evolving research trends in this domain (22).

In healthcare services, internet-based peer education has emerged as a promising intervention. For instance, continuous peer education via online platforms has been applied to improve negative emotions, sleep quality, and self-care abilities among abortion patient (23). Similarly, “internet +” peer education models have effectively enhanced self-management behaviors and disease control in type 2 diabetes patients (24). These cases demonstrate the potential of digital peer support in complementing traditional healthcare.

However, a significant knowledge gap exists regarding the application of internet-based peer education in treating postpartum depression. While existing literature covers other populations and health issues, there is a lack of in-depth research on how such digital peer interventions can be tailored to address postpartum depression specifically within the Chinese context, leaving a critical area unexplored for optimizing mental health support in this vulnerable group.

This study aims to combine peer education with Internet-based intervention, maximize the advantages of two treatments, and explore a treatment approach that can effectively and fairly serve the PPD group, so as to benefit a wider range of population in the future.

The primary objective of the study is to investigate the efficacy of the Internet-based Peer Education (IPE) regarding changes in symptom severity compared to control group using Regular Health Education (RHE) during a 6 weeks intervention period and at the follow-up assessments at 12 weeks. Referring to previous evidence, we hypothesize that the IPE group will be superior compared to RHE group in reducing depressive symptoms directly after the 6 weeks of intervention, and at follow-up.

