#### Inclusion criteria

2.2.1

Patients who provide written consent will be included in the study if they meet the following criteria: (1) age 20–49; (2) meet the Diagnostic and Statistical Manual of Mental Disorders (DSM-IV) criteria for postpartum depression, diagnosed as PPD by a psychiatrist; (3) score of EPDS >12 points, score of HDRS17 > 7, ≤24; (4) volunteer to participate in this study, and can complete the scale evaluation; (5) the onset occurs within 12 months after childbirth.

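### Section 2.10 plans within-arm paired tests at p < 0.05 that do not compare IPE with RHE; drop them or mark them descriptive (minor)

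*Protocol article*

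**What the plan says.** Section 2.10 (Statistical analysis plan) pairs each between-arm test for continuous data with a within-arm test. Student's t-test comes with a "paired t test for within-group differences", and for non-normal data the Mann-Whitney test comes with its counterpart: "the Wilcoxon test for within-group differences would be used". One rule closes the section: "A two-tailed test will be conducted", and a p-value below "0.05 will be considered statistically significant". Nothing sets the within-arm tests apart from that rule or calls them descriptive.

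The same section also plans valid comparisons between arms. For categorical variables a chi-square "test will be used to examine the between-group differences", and the repeated measurements go into a GEE that includes "the interaction term between group and time points".

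The hypotheses are comparative. The Introduction states: "we hypothesize that the IPE group will be superior compared to RHE group in reducing depressive symptoms". It says the same for quality of life, self-management and adverse events. Entry under section 2.2.1 requires "score of EPDS >12 points, score of HDRS17 > 7, ≤24".

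**The concern.** A paired test in one arm asks whether that arm's scores changed from baseline. It makes no use of the randomised comparison and does not estimate IPE against RHE. The document itself gives reasons to expect improvement in both arms without any effect of IPE:

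- Everyone receives RHE (sections 2.1 and 2.6.5).
- Other treatment is allowed, including antidepressants through referral (section 2.6.6).
- Women enter on raised EPDS and HDRS17, so some regression to the mean is likely.
- The sample size section assumes that 28.3% respond on health education alone.

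With a large common improvement, both within-arm tests are significant and say nothing about IPE. With a moderate one, it is easy by chance for one arm to cross 0.05 and the other not, and a significant result in IPE beside a non-significant one in RHE is readily misread as an effect. At stake is what may be claimed for EPDS, WHOQOL-BREF, SEMCD and HDRS17 as a continuous score, above all if the between-arm result is null.

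**Working it through.** The plan states no figure on this point to reproduce, so the check asks how often the within-arm tests separate two arms that do not differ.

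**Inputs from the document.** Two-sided 0.05 (section 2.10); 38 evaluable and 44 enrolled per arm (section 2.9; 38 × 1.15 = 43.7). Section 2.10 plans multiple imputation, so both sizes are shown. Section 2.9's inputs do not themselves give 38 (they give 22 per arm, or 26 with continuity correction). That is a separate matter, and nothing here depends on it.

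**Assumption.** d is the mean change divided by the SD of the change, equal in both arms. The document gives no SD of change, so a range is used.

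**Formula.** In each arm the paired t statistic follows a noncentral t distribution with n − 1 degrees of freedom and noncentrality d√n. Let p be the probability that it is significant. With independent arms, exactly one is significant with probability 2p(1 − p), IPE alone with p(1 − p), and both with p². The expression 2p(1 − p) is largest at p = 0.5, where it equals 50%.

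| n per arm | d | d√n | p | exactly one | IPE alone | both |
|---|---|---|---|---|---|---|
| 38 | 0.3 | 1.85 | 0.437 | 49% | 25% | 19% |
| 38 | 0.5 | 3.08 | 0.851 | 25% | 13% | 72% |
| 38 | 0.8 | 4.93 | 0.998 | 0.5% | about 0.2% | 99.5% |
| 44 | 0.3 | 1.99 | 0.494 | 50% | 25% | 24% |
| 44 | 0.5 | 3.32 | 0.900 | 18% | 9% | 81% |
| 44 | 0.8 | 5.31 | 0.999 | 0.1% | under 0.1% | 99.9% |

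For example, at n = 38 and d = 0.3: 2 × 0.437 × 0.563 = 0.492. The table uses unrounded p.

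**Which d is plausible?** Take the 28.3% control response as a fall of at least half the baseline score b (the threshold in section 2.11). Assume normal changes and a common b. The mean fall is then b/2 − 0.574 × SD, where 0.574 is the normal quantile at 1 − 0.283 = 0.717.

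- b = 16, SD 5: 8 − 2.87 = 5.13, d = 1.03. The RHE arm alone is significant with probability of about 100% (n = 38).
- b = 16, SD 8: 8 − 4.59 = 3.41, d = 0.43, probability 73%. If IPE added nothing, exactly one arm would be significant in 2 × 0.725 × 0.275 = 40% of trials.
- b = 12, SD 8: 6 − 4.59 = 1.41, d = 0.18, probability 19%.
- b = 20, SD 8: 10 − 4.59 = 5.41, d = 0.68, probability 98%.

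Both b and the SD are assumptions; only the 28.3% and the 50% threshold come from the document.

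**Selection on entry scores.** A simulation (4,000 trials per setting, 38 per arm, no difference between arms) gave:

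- EPDS above 12, assumed source mean 7 to 12, SD 5, retest correlation 0.5 to 0.8: at least one arm significant in 57% to 100% of trials through selection alone.
- HDRS17 above 7 and up to 24, assumed mean 10 or 14, SD 5, correlation 0.5 or 0.7: 12% to 51% through selection alone, against about 10% by chance (1 − 0.95² = 9.75%). With a 2-point improvement common to both arms, this became 96% to 100%.
- The between-arm t-test on change was significant in 4.5% to 5.9% across all settings, as it should be.

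**The case against.** The strongest reply is that nothing valid is missing. Section 2.10 names between-arm tests for every data type and a GEE whose group-by-time term is the right contrast for change. Every hypothesis is comparative. The primary outcome is responder status, which is binary and goes to the chi-square test, so the paired tests do not touch it. Section 3.1 promises a conservative reading of the self-reported scales, and section 2.10 says that a statistical plan will precede analysis. All of this stands and keeps the point minor. It does not remove the point: the within-arm tests are stated, they share the significance rule, and the caution in section 3.1 is about self-report, not about within-arm testing.

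A reader might go further and infer that the trial means to claim efficacy from change within the IPE arm. The document does not support that; no section gives the within-arm tests such a role.

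Nor should a reader take 50% as the expected rate of discordant arms. It is the ceiling of 2p(1 − p), reached only near d = 0.3 at these sample sizes.

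The selection argument is also uneven. It is strong for EPDS and weaker for HDRS17, whose entry window is wide and capped. It does not apply directly to WHOQOL-BREF and SEMCD, which are not entry variables. For those two, a common shift would have to come from recovery over time, RHE or other treatment.

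**Conclusion.** The point holds as a minor one. Section 2.10 gives inferential status to tests that cannot answer the trial's question, although it also plans tests that can. The logical fault needs no assumption; its frequency does. If the arms do not differ and share a standardised change of 0.3 to 0.8, exactly one arm is significant in about 49% down to 0.5% of trials at 38 per arm, or 50% down to 0.1% at 44, and half of those favour IPE. At the upper end both arms are almost always significant, which is equally uninformative about IPE. The primary comparison is not invalidated. The exposure is confined to the continuous secondary scales and to HDRS17 if it is analysed as a score.

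**What to change.** In section 2.10, either remove the paired t and Wilcoxon tests or state that within-arm change is descriptive only, shown as mean change with 95% CI by arm and without a significance claim. Add one sentence: every claim about IPE on depression, quality of life and self-efficacy rests on the between-arm contrast (the between-arm test or the GEE group-by-time term) with its confidence interval. This needs no new data and no change in sample size, and it slightly reduces the analysis work. It can be written into the statistical plan that section 2.10 says will be drawn up before analysis.

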### Primary outcome

2.11

The response rate based on 17-item Hamilton Depression Rating Scale (HDRS17) score at week 6 is considered primary outcomes. Response rate is defined as the percentage resulting from the dividing of the scores at baseline from the difference between those of baseline and week 6. The response rate reaches or over 50%, the patient will be defined as a responder; otherwise, the other patients will be considered non-responders. The formula for calculating the response rate is as follows:

$$\text{Response Rate}=\frac{\left(\text{HDRS}17\;\text{score}\;\mathrm{at}\;8\mathrm{th}\;\text{week}-\text{HDRS}17\;\text{score}\;\mathrm{at}\;\text{baseline}\right)}{\text{HDRS}17\;\text{score}\;\mathrm{at}\;\text{baseline}}\times 100\%$$

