### Secondary outcome

2.12

(1) Edinburgh Postpartum Depression Scale (EPDS) (25). It is considered the most frequently validated instrument to screen for perinatal depression. The scale consists of 10 items, mainly concerning the factors like depression, anxiety, anhedonia and self-harm/suicide. Higher scores indicate more severe symptoms of postpartum depression.(2) World Health Organization Quality of Life Scale Brief (WHOQOL-BREF) (28). This standardized tool conceptualizes quality of life as personal perception. Physical health, psychological health, social interactions, and environment are the four dimensions that make up WHOQOL-BREF. There are three to eight items in per domain. Additionally, two generic questions on health satisfaction and overall quality of life (Q1 and Q2) are provided. With the exception of 3 items—pain and discomfort, the need for treatment, and negative feelings—each item is based on self-report and scored on a scale of one to five, with higher scores indicating higher quality of life.(3) Self-Efficacy to Manage Chronic Disease Scale (SEMCD) (29). This patient reported scale mainly evaluate symptoms of chronic conditions, functioning, and self-management. This self-efficacy scale for chronic disease patients was developed by Stanford University in the United States. The scale contains 6 items, each item ranging from 1 to 10, with 1 indicating no confidence at all and 10 indicating great confidence. The average score of the 6 items reflected the average level of self-efficacy of patients. A score of 1–3 indicates a low level of self-efficacy, a score of 4–7 indicates a medium level of self-efficacy, and a score of 8–10 indicates a high level of self-efficacy. Its Cronbach’sα coefficient is 0.91, with high reliability and wide application.

Scales information will be collected and managed by corresponding researchers, who are unaware of the group division. To exclude confounding factors, each subject will be evaluated by the same researcher in the duration of trial.

Evaluation time points: all scales will be evaluated at baseline, 1, 2, 4, 6, and 12 weeks after the initiation of intervention.

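### Per-visit comparisons of the continuous scales switch between a t-test and a rank test on the look of the data, beside a GEE that needs no switch but is not named as deciding

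*Protocol article*

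**What the plan says.** Section 2.10 (Statistical analysis plan) of the protocol article sets a rule with two branches. The first begins "For continuous and normally distributed data, we performed Student’s" and leads to the t-test, with means and standard deviations. The second reads "If data were distributed nonnormally, the Mann–Whitney U test for between-group differences", with the Wilcoxon test as its within-group counterpart. Its descriptive summary is given as "Nonnormally distributed data would be expressed as the median or interquartile range (IQR". The section names no normality test or threshold.

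The same section adds, without limiting it to any outcome or model, "Missing data will be handled using the multiple imputation method".

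For the repeated measurements, it also says that "the Generalized Estimating Equations (GEE) model will be employed". This model has group, six categorical time points and their interaction, plus covariates for imbalanced baseline characteristics. It is not conditional on normality. The text does not say whether it replaces the two-group tests or which result is to be relied on.

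Section 2.12 (Secondary outcome) shows the reach of the rule: "all scales will be evaluated at baseline, 1, 2, 4, 6, and 12 weeks after the initiation of intervention". The primary outcome in section 2.11 is binary ("The response rate reaches or over 50%, the patient will be defined as a responder") and goes to the chi-square test, outside this rule.

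**The concern.** A t-test compares means. A Mann-Whitney test compares the two distributions by rank and equals a comparison of medians only when the shapes match. If the distribution picks the test separately at each visit, the question being answered can change along one scale's time course, for instance means at week 2 and ranks at week 6. The rank branch names no between-arm estimate or interval, so nothing is specified for combination over imputations.

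The stake is how the severity, quality-of-life and self-efficacy results are reported. The Conclusion also says that the trial will supply data for power calculations for a larger study. Mean differences and standard deviations serve that use directly; a U statistic beside two medians does not.

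**Working it through.** **1. How many comparisons the rule can reach.** EPDS (1), WHOQOL-BREF domains (4), SEMCD (1) and the HDRS17 score (1) make 7 scores. With five post-baseline visits (T1 to T5, section 2.8), 7 × 5 = 35 between-arm comparisons are open to the rule if all are tested. The article does not list which will be.

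**2. Can the branch change between visits?** Entry criteria truncate the baseline scores (EPDS above 12; HDRS17 above 7 and at most 24). Section 2.9 assumes 28.3% versus 70% responders at week 6. On those assumptions the distributions should change shape over time and differ between arms.

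As an illustration, rounded scores on 0 to 30 with mean 10 and right skew (gamma shape 2 to 8) were simulated at 44 per arm, 4,000 trials per shape. The rank test was chosen if Shapiro-Wilk gave p < 0.05 in at least one arm. The rule sent 69% to 99% of comparisons to the rank test. For two visits with the same shape and independent verdicts, the chance of landing in different branches is 2p(1 − p):
- p = 0.69: 2 × 0.69 × 0.31 = 0.43
- p = 0.99: 2 × 0.99 × 0.01 = 0.02

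Positively correlated verdicts would lower these figures. The shapes are assumptions.

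**3. Does switching harm the error rate?** In the same simulations the plain t-test rejected in 4.5% to 5.2% of null trials and the switching rule in 4.7% to 5.5%. Simulation error at 4,000 trials is about ±1.96 × √(0.05 × 0.95 / 4,000) = ±0.7 percentage points. No inflation is shown. Equally, the switch buys no error control that the t-test lacked.

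**4. What if normality is judged after imputation?** With 15% missing, 0.15 × 44 = 6.6, so about 7 values per arm are imputed and 37 observed. Assumptions: normal-model imputation, Shapiro-Wilk at 0.05 in both arms, 400 simulated trials per setting. Share of single comparisons in which some imputed copies select the t-test and others Mann-Whitney:

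| Score shape | 5 imputations | 20 imputations |
|---|---|---|
| Normal | 25% | 47% |
| Mild skew | 40% | 65% |
| Stronger skew | 33% | 50% |

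Simulations with other assumed shapes took the upper end to about 75%. The range of about 25% to 75% illustrates the problem and is not a bound. Other shapes can fall outside it, and the share is zero if normality is judged once, on the observed data.

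**5. What can be pooled?** Rubin's rules average an estimate Q over the M imputed data sets and use total variance T = W + (1 + 1/M)B, where W is the mean within-imputation variance and B the between-imputation variance. Each data set must supply an estimate and a standard error.
- t-test: mean difference and its SE, so poolable.
- Mann-Whitney as named: U and a p-value, with a median or IQR per arm beside it; no estimate is named.
- GEE as planned: the group effect plus the group-by-visit term, with its SE, at each visit, so poolable whatever the distribution.

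**The case against.** The strongest reply is that the GEE already does the work. It is in the same section, does not depend on normality, and gives a between-arm contrast with a standard error at every visit. This stands. A reader might infer from the switching rule that the continuous outcomes as a whole would lack effect estimates or change target between visits; the GEE rules that reading out. What remains is that both analyses are kept and neither is put first, so the switched tests could supply the reported result.

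Three other replies also hold:
- The article does not say that normality is judged in each imputed data set. That step, the number of imputations and the pooling details may properly sit in a fuller analysis plan, so the figures in step 4 are conditional.
- A rank test is not beyond pooling. A Hodges-Lehmann shift, or U/(n1 × n2) with its standard error, could be combined. The sentence on medians and IQR says how data are described and does not forbid such an estimate; the plan simply names none.
- The rule is written down in advance and the statisticians are blinded, so this is not a free choice of test after seeing the results by arm.

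**Conclusion.** The concern holds for the per-visit between-arm comparisons of EPDS, the WHOQOL-BREF domains, SEMCD and the HDRS17 score. The article states a data-dependent rule that can mix mean and rank comparisons within one scale and names no between-arm estimate in its rank branch. It sets this beside a GEE that avoids both problems but is not given priority. Conflict between imputed data sets is a further possibility only if normality is judged after imputation.

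Two stronger readings should be resisted. The week-6 responder analysis is binary and untouched. Nor do the simulations show false-positive inflation from switching; the harm is in what gets estimated and reported. Severity is minor, because these are secondary analyses. It is a cheap improvement.

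**What to change.** Remove the normality switch as the basis for between-arm inference. State that, for every continuous scale, the deciding analysis is the planned GEE with identity link. Its outcomes are the post-baseline visits T1 to T5, with arm, visit and arm-by-visit, adjusted for that scale's own T0 value. T0 thus moves from being one of six outcome time points to a covariate. Report the between-arm mean difference at week 6 and at T5 with a 95% CI, pooled over the imputations. Keep t-tests or rank tests, if wanted, only as labelled sensitivity analyses. Medians and IQR can stay as descriptive summaries.

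The cost is a few sentences in section 2.10 and minor analysis work. No change to data collection, visits or sample size is needed.
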